#### Power for SBP rate of change

Power was calculated, examining the rate of change, including all three waves in the analyses. The following assumptions were used: R = 0.90 (reliability); pooled σ = 20.75; δ = 5, 6, 7 (SBP point reduction per year in the intervention groups relative to the UHC group reduction); d = δ/σ (where δ is point reduction per year and d is Cohen’s d for the rate of change); ρ = 0.6 is the average correlation between baseline and follow up assessments; Tn = 3 time points (baseline, 3 month and 12 month). The formulas from Diggle, Liang and Zeger (1994) were used [39]: the power calculation demonstrates that under ITT, we can detect a rate of reduction in SBP equivalent to 5.40 mmHg which translates to relatively small effect sizes using Cohen’s d. It is also noted that the assumed standard deviation was conservatively posited to be quite large (pooled estimate of around 21). If a smaller standard deviation is observed, power will be greater. Thus, a sample size of 165 per group was proposed.

For the non-linear, longitudinal change sensitivity analyses [40], the assumptions were the same as above, and an endpoint reduction in SBP of 6 points was posited. Assuming a non-linear decline function and differential treatment effects, power was greater than 0.80 to detect small effects (for example, a 0.5 point reduction) in one intervention group at 3 months and medium to large effects (2.5 to 5 point reduction in SBP) in the second group at 3 months, with a net reduction of 6 points by study end in both groups.

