### Eligibility and inclusion/exclusion criteria

A total of 495 black and Hispanic patients (≥21 years of age) who have had a first time or recurrent stroke (ischemic or hemorrhagic) or transient ischemic attack (TIA) and have uncontrolled SBP will be recruited: 165 randomized to each group. To be eligible a patient also needs to be English or Spanish speaking and have a telephone to use for intervention encounters. Patients are excluded if they have a clinical condition that may require specialized HTN management (for example, end stage renal disease, severe HF). Additional inclusion/exclusion criteria are listed in Table 2.

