### Statistical analysis plan

#### Data analyses for primary outcome: SBP

The main hypothesis is that those assigned to the intervention groups will, on average, exhibit greater 3-month and 12-month decreases in SBP than those assigned to the usual care condition. The primary proposed analyses will use mixed random effects models, and a full information maximum likelihood (FIML) approach, with sensitivity analyses using generalized estimating equation (GEE) regression models. The change from pre- to post-treatment values of SBP will be modeled as functions of time, treatment and the interaction of time and treatment. The general longitudinal mixed effects model, using SAS PROC MIXED (SAS, Cary, NC, USA), will be used to model serial correlations and group heterogeneity in residual variances if needed. The intent-to-treat (ITT) analyses will permit all individuals with at least one observation to be included. If a non-linear pattern of change is observed, non-linear models will be used in sensitivity analyses.

Prior to analyses, baseline values of all variables will be examined in order to determine if any covariates require modeling due to imbalance among groups. Examination of baseline differences on key variables between completers and those lost to follow up will be conducted to inform about the nature of the missing data.

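### The power above 0.80 is attributed to 3-month SBP effects of 0.5 and 2.5 to 5 points, but the stated inputs support it only for the trajectory or 12-month effect ending at 6 points

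*Protocol article*

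**What the plan says.** Under *Power for SBP rate of change*, the protocol article first gives a main calculation for the rate of change over three waves. Its inputs are "pooled σ = 20.75", a reliability R of 0.90, "ρ = 0.6 is the average correlation between baseline and follow up assessments" and three time points (0, 3 and 12 months). It reports a detectable reduction of 5.40 mmHg and settles on 165 per group.

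A second paragraph covers non-linear sensitivity analyses. It keeps the same assumptions and posits a reduction of 6 points at the endpoint. It then states that "power was greater than 0.80 to detect small effects (for example, a 0.5 point reduction) in one intervention group at 3 months". For the other intervention arm, the same claim of power is made for what the article calls "medium to large effects (2.5 to 5 point reduction in SBP) in the second group at 3 months". The sentence closes by saying that both arms end the study 6 points lower.

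Under *Data analyses for primary outcome: SBP*, the main hypothesis is that the intervention groups show "greater 3-month and 12-month decreases in SBP than those assigned to the usual care condition". The primary outcome section likewise names SBP change at both 3 and 12 months.

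**The concern.** As written, the thing detected with power above 0.80 is a 0.5-point difference at 3 months. That is about a quarter of the standard error of a two-arm comparison with 165 per arm, so no trial of this size could detect it. The main calculation concerns the yearly rate of change, which leaves this sentence as the article's only statement about power at 3 months.

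Because 3-month change is part of the primary outcome, a reader could take the sentence as assurance that small early effects will be seen, and could misread a null 3-month result.

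**Working it through.** **Inputs from the article.** "165 randomized to each group"; SD 20.75; correlation 0.6; R = 0.90; comparison of each intervention arm with usual home care; effects of 0.5, 2.5 and 5 points at 3 months and 6 points at 12 months.

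**Assumptions.** Alpha, sidedness and dropout are not stated. I use two-sided 5%, target power 80% (multiplier 1.960 + 0.842 = 2.80), no loss, and equal correlation between all visits. The article does not say how R enters; I divide the variance by R and also show results without it.

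**1. The 5.40 mmHg of the main calculation.** A baseline-adjusted contrast at one follow-up gives 2.80 × 20.75 × √((1 − 0.6²)/0.90) × √(2/165) = 5.40, which matches and supports this use of R. A rate-of-change formula with times 0, 0.25 and 1 year, without R, gives 5.50, or 78.5% power at 5.40.

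**2. Standard error of the 3-month contrast.**
- Change score: 20.75 × √(2 × 0.4) × √(2/165) = 2.04; with R, 2.04/√0.90 = 2.15.
- Baseline-adjusted: 20.75 × √(1 − 0.36) × √(2/165) = 1.83; with R, 1.93.

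**3. Power of the 3-month contrast.** Power = Φ(δ/SE − 1.96) + Φ(−δ/SE − 1.96).

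| 3-month effect | Change score | Change score, R = 0.90 | Baseline-adjusted | Baseline-adjusted, R = 0.90 |
|---|---|---|---|---|
| 0.5 | 5.7% | 5.6% | 5.9% | 5.8% |
| 2.5 | 23% | 21% | 28% | 25% |
| 5 | 69% | 64% | 78% | 74% |

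One-sided 5% gives about 8% to 9% for 0.5 points. For 5 points it gives 75% to 79% by change score and 83% to 86% baseline-adjusted. Reaching 80% power for 0.5 points at two-sided 5% would take about 17,300 (baseline-adjusted) to 21,600 (change score) per arm without R. Dividing by 0.90 raises this to about 19,200 to 24,000.

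**4. Detectable 3-month difference at 80% power.** This is 2.80 × SE: with R, 5.4 (baseline-adjusted) and 6.0 (change score); without R, 5.1 and 5.7.

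**5. Where power above 0.80 can come from.** Take 0.5, 2.5 and 5 as the 3-month point on a path that ends at 6 points.
- 12-month contrast of 6 points: 84% (change score) and 91% (baseline-adjusted); with R, 80% and 88%.
- Joint 2-df test of 3 and 12 months, one arm against usual care, without R: 0.84 to 0.88 for the path (0.5, 6), 0.76 to 0.85 for (2.5, 6), 0.81 to 0.92 for (5, 6). With R the lowest value is 0.71.
- Joint 4-df test over three arms, without R: 0.86 to 0.98.
- Linear slope test, without R: 0.89, 0.83 and 0.71 for the three paths.

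On the 0.5-point path, the 3-month difference alone has about 6% power and the 12-month difference alone has 80% to 91%. The stated power is supplied by month 12.

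**The case against.** The strongest defence is context. The section concerns rate of change, the paragraph concerns longitudinal models, and the sentence ends with 6 points in both arms by study end. The opening of *Methods/Design* also says that scenarios with different effect sizes per arm would be examined for non-linear change. On that reading the 3-month values only describe the shape of the path, and the stated power broadly reproduces. This stands: a reader might infer an arithmetic error, but the article does not show one. It does not rescue the sentence, whose wording still makes the 3-month effect the thing detected.

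Three further inferences are tempting and unsupported.

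- **That the effect-size labels are wrong.** Dividing the raw 3-month points by 20.75 gives d = 0.12 to 0.24 for 2.5 to 5 points, far from medium or large. But the section defines d on the reduction per year. Annualised, 2.5 to 5 points in a quarter year is 10 to 20 per year, so d = 0.48 to 0.96; 0.5 points is 2 per year, d = 0.10. The labels fit that definition, although the paragraph does not say that they are annualised.
- **That the trial is underpowered for every 3-month effect named.** This is clear for 0.5 and 2.5 points. At 5 points it depends on the unstated alpha: a one-sided, baseline-adjusted test exceeds 80%.
- **That linear change at 5.40 per year leaves almost no power at 3 months.** A quarter of the slope has a quarter of the slope's standard error, so under a linear model the 3-month effect is tested with the slope's own power.

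It is also fair that the 165 per group rests on the main calculation, so the sample size does not depend on this sentence.

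**Conclusion.** The point holds as a fault of attribution. On the article's own inputs, with two-sided 5% and no attrition assumed, the 3-month contrast has about 6% power for 0.5 points, 21% to 28% for 2.5, and 64% to 78% for 5. No choice of sidedness, baseline adjustment or handling of R brings 0.5 points above 9%. The result at 5 points is marginal and depends on alpha. With 20% loss (an illustrative rate), it falls to 59% to 69% without R.

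A figure of about 0.80 or more is recoverable only for the trajectory or 12-month difference ending at 6 points, and there only broadly: some joint and slope tests fall to about 0.71. The article therefore states a 3-month power that the design does not have, for part of its primary outcome. The sample size, the 5.40 mmHg figure and the planned analysis are not called into question by this.

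**What to change.** Reword the second paragraph of *Power for SBP rate of change*:

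- Say that the power above 0.80 refers to the trajectory, or to the 12-month difference of 6 mmHg, and name the test used. Present the 3-month values as the assumed shape of the path.
- State alpha and sidedness.
- Report separately the 3-month difference detectable with 80% power. At two-sided 5% and before attrition, this is about 5.4 mmHg baseline-adjusted and 6.0 as a change score with R = 0.90, or 5.1 and 5.7 without R.
- Keep the effect-size labels if they are annualised, and say so.

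The cost is one reworded paragraph and a less favourable statement of 3-month power. Neither the design nor the sample size needs to change.

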## Discussion

The cumulative 5-year risk of having a recurrent stroke after a person’s first-ever stroke is over 30%, and the 30-day fatality risk associated with secondary strokes has been reported to be 40 to 50%, which is significantly higher than first stroke fatality rates [41,42]. Blacks and Hispanics have higher risk of recurrence than whites [5,7,8]. A contributor to this ongoing risk of stroke survivors is ineffective recurrent stroke preventive interventions. Our interventions are designed to specifically address HTN, a major risk factor for strokes and recurrent strokes, and are built on NP and HC models found to be successful in addressing other clinical conditions and established in other care settings. The NPs are positioned to complement UHC services by assessing and addressing hospitalization risk factors that are common during transitional care periods, while also providing a specific HTN management intervention geared toward preventing stroke recurrence. Both the NP and NP + HC interventions expand on the usual transitional care focus, which is on hospital discharges and preventing rehospitalization, by focusing on longer-term stroke risk prevention, community provider connections to facilitate long-term chronic care management, and reintegration into the community.

Our interventions were informed by models that showed promise in other settings. Focus groups and individual interviews were also conducted with black and Hispanic post-stroke patients who had received home care and their caregivers to further inform our intervention approach along with our enrollment efforts. During these focus groups, post-stroke patients expressed fear of research and lack of trust in researchers. They suggested we might counter these fears by making sure that potential patients are able to get a very clear understanding of the study and their expected involvement. Operationally, this led us to simplify the language used in describing the study: for example, the randomization process (including being clear about the possibility of being placed in the usual care group) and the intent of the interventions. We also built more time into the recruitment calls and in-person consenting process so that the patients are free to ask all their questions. In addition, field staff were trained in the ‘teach back’ method - asking patients to describe in their own words what the initiative was about and what their commitment was in order to determine areas that needed further clarification. Lastly, we incorporated the suggestion of focus group members that we stress the useful knowledge gained through research and how patients are the ones with the important information.

The intervention approach already stressed patient-centeredness in goal setting, but focus group findings led us to enhance staff training to further address the cultural issues that came up at our meetings. For example, to address the issue of trust or rather distrust in the medical care systems, we instituted staff discussions and practice sessions on how to maintain trust (for example, reflective listening, following up with community referrals when requested, addressing other clinical conditions if priority to the patient). Some of our focus group participants also expressed a sense of inevitability to their stroke experience and the possibility of having another stroke. These feelings seem to have been influenced partly by the view that chronic disease, hypertension, and diabetes are ‘passed down’ in the family. During our staff training, we discussed the implications of these beliefs (for example, how they may impact a person’s self-management behavior), how to identify these beliefs, and how to address them (for example, additional education). We also were guided by our participants to engage family and others who provided the patient’s primary social support if the patient indicated that this was desirable, to take the time to address medication administration and side effect questions and to explore patients’ attitudes and beliefs about medications - elements all integrated into the intervention approach. Additional direction for intervention staff on how to recognize depression and isolation risk was provided in the training as these were areas that our focus group informants felt could hinder adherence to recommended management guidelines and their recovery.

Two significant issues related to BP criteria for patient eligibility arose shortly before and after enrollment began, and both had potentially significant operational implications. A few weeks before launch the Program Advisory Committee for the Center for Stroke Disparities Solutions (CSDS) [43], parent of our study, advised the team to modify the BP eligibility screening process. Initially, the protocol was designed to determine patient eligibility based on a single face-to-face encounter in which the average of 3 SBP readings needed to be ≥ 140 mmHg after the patient passed other eligibility screening questions described above. The revised protocol calls for 2 face-to-face interviews in which 3 BP readings are taken and need to result in an average SBP of ≥ 140 mmHg in both interviews. Currently, there is no widely accepted scientific standard for enrolling patients in BP studies; some use historical data in medical records to identify potential study subjects [44,45], some enroll patients if they simply have a HTN diagnosis [46], some allow enrollment of those in pre-HTN stage [47], others adopt a higher SBP threshold of ≥ 150 mmHg at the time of enrollment [48] and some include patients with single BP measurements in the uncontrolled HTN range [49,50]. The intent of the more stringent screen employed by our trial is to increase the likelihood of enrollment of the intended target population - those with uncontrolled HTN. Adjustments to our workflow and budget were implemented, although it was unclear how many people would drop out after the second BP screening visit. Data from this revised screening process will help to inform future studies. As of 5 September 2014, of the 97 patients who passed the first BP screen, 65 (67%) met the SBP threshold at the second BP screen.

The second BP threshold issue that came up shortly after enrollment began derived from publication of the 2014 Evidence-Based Guideline for the Management of High Blood Pressure in Adults [51]. One of the 9 recommendations made is to treat to a goal of SBP < 150 mmHg for the general population aged 60 years and over, a departure from the prior guideline [52], which recommended the SBP goal of < 140 mmHg for all patients. None of the new recommendations addressed the goal SBP for post-stroke patients. We expect that around 60% of the patients enrolled in our study will be aged 60 years or over. Since there is a body of evidence showing the benefit of lower SBP for stroke risk reduction, and after a discussion with HTN specialists at the Center for Stroke Disparities Solutions, we did not alter our intervention approach to increase our SBP target to < 150 mmHg. However, there is some concern that primary care providers overseeing the long-term care of these patients may be influenced by these published guidelines and decline to more aggressively treat patients with SBP levels between 140 and 149 mmHg.

Results of this trial will provide important information on the design of interventions to address treatment gaps and disparities in recurrent stroke prevention for vulnerable black and Hispanic populations. The trial focuses on care transitions, a juncture when patients are particularly susceptible to adverse events. The interventions are innovative in adapting for stroke patients an established transitional care model shown to be effective for HF patients, pairing the professional NP with a HC, tailoring the interventions for black and Hispanic patients respectively, and placing primary emphasis on longer-term risk factor reduction and community reintegration rather than shorter-term transitional care outcomes.

## Trial status

Patient enrollment began in January 2014. Enrollment period is expected to be 30 months.

## Abbreviations

ADL: activities of daily living
AHA: American Heart Association
ASA: American Stroke Association
BECCI: Behavior Change Counseling Index
BP: blood pressure
BMQ: beliefs about medications
CSDS: Center for Stroke Disparities Solutions
CTI: Care Transitions Intervention®
CTIs: Community Transitions Interventions
EHR: electronic health record
EuroQol: health-related quality of life
FAB: Frontal Assessment Battery
FIML: full information maximum likelihood
GEE: generalized estimating equation
HC: health coach
HF: heart failure
HTN: hypertension
ICD-9: International Classification of Diseases, version 9
IPAQ: International Physical Activity Questionnaire
ITT: intent-to-treat
MINT: Motivational Interviewing Network of Trainers
NP: nurse practitioner
PCP: primary care provider
OASIS: Outcomes Assessment and Information Set
PACIC: Patient Assessment of Chronic Illness Care
RCT: randomized controlled trial
SBP: systolic blood pressure
TCM: Transitional Care Model
TIA: transient ischemic attack
UHC: usual home care
UHC + NP: usual home care complemented by a nurse practitioner
UHC + NP + HC: usual home care complemented by a nurse practitioner plus health coach
VNSNY: Visiting Nurse Service of New York
